#### 8.1.2 Secondary study parameters/endpoints

##### **Efficacy**

|                           |                                                                                                                                                                                                                                                                                                                                                                                               |
|---------------------------|-----------------------------------------------------------------------------------------------------------------------------------------------------------------------------------------------------------------------------------------------------------------------------------------------------------------------------------------------------------------------------------------------|
| Hospital admission        | 
 
Length-of-stay in hospital
 
ICU admission within 7 days (excluding subjects receiving protocolized vasopressor therapy)
 
                                                                                                                                                                                                             |
| New onset organ failure   | Any of the following within 48 hours: 
 
Rise in SOFA score of at least 2
 
Organ support (i.e. vasopressor use [non-]invasive mechanical ventilation, acute dialysis, ECMO)
 
                                                                                                                                                            |
| Fluid resuscitation       | 
 
Volume of IV fluid resuscitation within three hours (including prehospital fluids administered)
 
Volume of IV fluid resuscitation within 7 days
 
Fluid balance within three hours (i.e difference between volume of intravenous plus oral fluids and the volume of fluid output (i.e. urine output and other fluid losses))
 
 |
| Hemodynamic resuscitation | 
 
Time to recovery of normal perfusion/hemodynamic stability (HDS)*
 
Proportion of patients reaching normal perfusion/hemodynamic stability* within three hours
 
                                                                                                                                                                       |

\* Hemodynamic stability (HSD) is defined as MAP  $\geq$  70 mmHg. SBP  $\geq$  90 mmHg, lactate  $\leq$  4 mmol/L and SI  $\leq$  0.9.

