## 5. TREATMENT OF SUBJECTS

### 5.1 Investigational product/treatment

#### Intervention:

The investigational product in this study is the Starling SV monitor, which is a medical device manufactured by Baxter Healthcare. The Starling SV monitor is a non-invasive hemodynamic monitor that provides real-time continuous information about stroke volume index, cardiac index, cardiac output, and total peripheral resistance. In this intervention study, the Starling SV monitor is designed to assist in guiding hemodynamic resuscitation for patients with sepsis.

In the experimental group, patients will receive hemodynamic resuscitation guided by the Starling SV monitor. A dynamic assessment of fluid responsiveness using the monitor will be performed at every clinical decision point during the first three hours of study enrolment.

Vital parameters, including blood pressure and heart rate, are measured upon ED arrival (triage), immediately after administration of a fluid bolus and at least twice per hour during the first 3 hours. Lactate will be measured at ED arrival (triage) and will be repeated every two hours as long as lactate is  $> 4$  mmol/L. Fluid responsiveness will be measured by the Starling SV monitor immediately before and after the administration of fluids. Fluid responsiveness is defined as an increase in stroke volume index by at least 10% after a fluid bolus of 500 mL in 10 min.

First, we will perform the first measurement during the first administration of 500 mL of IV fluids. During both the fluid bolus, we will measure the change in stroke volume index ( $\Delta$ SVI) using the Starling SV and use the stroke volume index change in response to the fluid bolus to determine fluid responsiveness.

If, at any time during the first 3 hours, patients have: (see figure 1)

- MAP  $< 65$  mmHg or systolic blood pressure  $< 90$  mmHg:
  - Fluid responsive (on last measurement): patients will receive (another) 500 mL of IV fluids if considered fluid responsive (and a new Starling SV measurement will be obtained). Reassess after intervention.
  - Not fluid responsive (on last measurement): patients will receive vasopressor (noradrenaline), according to the standard care protocol.\*
- MAP  $\geq 65$  mmHg or systolic blood pressure  $\geq 90$  mmHg combined with SI  $> 0.9$ :

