  - Fluid responsive (on last measurement): patients will receive (another) 500 mL of IV fluids if considered fluid responsive (and a new Starling SV measurement will be obtained). Reassess after intervention.
  - Not fluid responsive (on last measurement): repeat measurement in 30 minutes.
    - If (MAP  $\geq 65$  mmHg and systolic blood pressure  $\geq 90$  mmHg) combined with SI  $> 0.9$ : optional 500 mL of IV fluids based on rescue rules. Reassess after intervention;
    - If MAP  $< 65$  mmHg or systolic blood pressure  $< 90$  mmHg: see above;
    - If (MAP  $\geq 65$  mmHg and systolic blood pressure  $\geq 90$  mmHg) combined with SI  $\leq 0.9$ : see below.
- MAP  $\geq 65$  mmHg and systolic blood pressure  $\geq 90$  mmHg, combined with SI  $\leq 0.9$ : no action needed.

Rescue fluids (500 mL of IV fluids) recommended if, at any time during the first 3 hours, patients have any of the following conditions:

- Severe hypotension (systolic blood pressure  $< 70$  mmHg or MAP  $< 50$  mmHg)

- Refractory hypotension (systolic blood pressure < 90 mmHg or MAP < 65 mmHg) with administration of noradrenaline at dose of 20 mcg/min or of an equivalent dose of another vasopressor)
- Lactate level > 4 mmol/liter and increasing after 2 h of therapy
- Sinus heart rate > 130 beats/min for > 15 min
- PoCUS evidence of extreme hypovolemia

All fluids administered will be balanced fluids. In addition to the fluid resuscitation as described above, all patients will receive a standard 1.5 L per day of IV fluids from the moment of ED arrival. The total volume of IV fluids will be limited to a maximum of 60 ml/kg over three hours to prevent hypervolemia.

\* Vasopressor therapy initiated according to personalized protocol will be performed in the stepwise approach of standard care. Every 30 minutes vital parameters will be repeated. According to the protocol it can be that vasopressor therapy needs to be increased or that fluids will be administered, as vasopressors can cause fluid responsiveness due to increased venous return.

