#### Control:

Vital parameters, including blood pressure and heart rate, are measured upon ED arrival (triage), immediately after administration of a fluid bolus and at least twice per hour during the first 3 hours. Lactate will be measured at ED arrival (triage) and will be repeated every two hours as long as lactate is > 4 mmol/L. No required therapeutic protocol will be mandated for patient treatment, which will be determined at the discretion of the physician and in accordance with hospital standards.

All fluids administered will be balanced fluids. In addition to the fluid resuscitation as described above, all patients will receive a standard 1.5 L per day of IV fluids from the moment of ED arrival. The total volume of IV fluids will be limited to a maximum of 60 ml/kg over three hours to prevent hypervolemia.

The purpose of the control group is to compare the outcomes of hemodynamic resuscitation guided by the Starling SV monitor in the experimental group with the outcomes of standard care in the control group.

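### The ICU-admission endpoint excludes patients by a treatment given after randomisation, and on the likeliest reading it does so in the guided arm only

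*Protocol*

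**What the plan says.** Protocol section 8.1.2 (Efficacy table, hospital admission row) defines the endpoint as "ICU admission within 7 days (excluding subjects receiving protocolized vasopressor therapy", closing the bracket after these words. The term *protocolized* is not explained there or elsewhere.

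Section 5.1 gives vasopressor rules by arm:

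- **Guided arm.** For a patient with MAP below 65 mmHg or systolic pressure below 90 mmHg, the rule is "Not fluid responsive (on last measurement): patients will receive vasopressor (noradrenaline), according to the standard care protocol". A footnote adds: "Vasopressor therapy initiated according to personalized protocol will be performed in the stepwise approach of standard care".
- **Control arm.** "No required therapeutic protocol will be mandated for patient treatment, which will be determined at the discretion of the physician". Section 3 (Groups) makes clear that control patients may also receive vasopressors.

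Section 1 says that under current care vasopressors may be started at the ICU. Section 9 makes the intention-to-treat population the analysis population for both primary and secondary endpoints. Section 9.2 tests secondary endpoints at p < 0.05 whatever the primary result, and leaves the methods for binary endpoints to a later plan.

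The next row of the same table counts as new-onset organ failure within 48 hours "Organ support (i.e. vasopressor use [non-]invasive mechanical ventilation, acute dialysis, ECMO", with no exception for vasopressors that the algorithm prescribes.

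**The concern.** Receiving noradrenaline under the algorithm happens after randomisation and is a result of the assigned strategy. Leaving those patients out of an outcome breaks the comparison that randomisation protects. If the exclusion works in one arm only, it removes a selected group there (hypotensive patients whose stroke volume index did not rise after a bolus), while their control counterparts remain. Two equivalent strategies would then show different ICU rates.

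ICU admission matters to patients and is among the efficacy endpoints of a trial whose primary endpoint is a fluid volume. A lower ICU rate in the guided arm would readily be read as clinical support for the monitor, and part or all of it could come from the definition.

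**Working it through.** **Step 1: to whom does the exclusion apply?** Only the guided arm has a study rule that triggers a vasopressor, and the footnote in section 5.1 ties it to the personalised protocol. The control arm has no mandated protocol. Guided-arm-only is therefore the likeliest reading. It is not certain, because section 5.1 also says that the noradrenaline follows a standard care protocol.

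**Step 2: inputs.** The protocol states no figure for this endpoint, so there is none to reproduce. From section 4.4: 94 patients per arm. Assumed, because the protocol gives none of them:

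- p, the true ICU rate, equal in both arms: 20%
- v, the share of the guided arm excluded: 10% or 15%
- pv, the ICU risk among those excluded: 60% or 80%

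**Step 3: formulas.** The text does not say whether excluded subjects leave the denominator or only have their admission ignored.

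- Removed from the denominator: (p − v·pv)/(1 − v)
- Counted as non-events: p − v·pv

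**Step 4: results against 20% in control.**

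| v | pv | Removed | Ratio | Non-event | Ratio |
|---|---|---|---|---|---|
| 10% | 60% | (0.20 − 0.06)/0.90 = 15.6% | 0.78 | 14.0% | 0.70 |
| 10% | 80% | (0.20 − 0.08)/0.90 = 13.3% | 0.67 | 12.0% | 0.60 |
| 15% | 80% | (0.20 − 0.12)/0.85 = 9.4% | 0.47 | 8.0% | 0.40 |

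In patients, the first row removes 9.4 of 94 guided patients and 5.6 of 18.8 admissions, leaving 13.2/84.6. The last row is an extreme case: 0.12/0.20 = 60% of guided-arm ICU admissions would have to come from excluded patients.

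**Step 5: direction.** Under removal, the reported rate falls below p exactly when pv > p. Under the non-event reading it falls whenever any excluded patient is admitted. Section 1 makes pv > p plausible, since in current care starting a vasopressor can itself mean going to the ICU.

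**Step 6: chance of a false positive.** Assume v = 10%, ICU risk 100% in patients on early vasopressors and 10% in the rest. Then p = 0.10 × 1.00 + 0.90 × 0.10 = 19.0% in both arms, and the guided arm is reported as 10.0% (removed) or 9.0% (non-event). The chance of p < 0.05 in favour of the guided arm is Φ((Δ − 1.96·SE0)/SE1), with SE0 pooled and SE1 unpooled:

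- Removed (94 vs 84.6): (0.090 − 1.96 × 0.0531)/0.0520 = −0.27, which gives 39%
- Non-event (94 vs 94): (0.100 − 1.96 × 0.0506)/0.0501 = 0.02, which gives 51%

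With v from 5% to 20%, ICU risk 70–100% on early vasopressors and 5–15% otherwise, the spurious difference runs from about 3 to 20 percentage points.

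**The case against.** **The exclusion has a sensible purpose.** If vasopressors are normally started at the ICU, the algorithm may cause transfers made only to give protocol noradrenaline, and the authors plausibly did not want to count these as deterioration. That aim is fair. The text, however, excludes the subjects, so every ICU admission of theirs over 7 days is lost, whatever its reason.

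***Protocolized* may cover both arms.** A reader might take it as settled that such patients exist only in the guided arm. The documents do not go that far: the term is undefined and a standard care protocol is mentioned. Guided-arm-only is the likeliest reading, no more. Under a both-arms reading the one-sidedness goes, but the endpoint would still condition on a treatment that the intervention changes.

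**The later plan may deal with it.** Section 9.2 defers methods for binary endpoints, and that plan is not at hand. The exclusion, however, is part of the endpoint definition in the protocol.

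**The sizes are assumed.** This stands. They are illustrations, not estimates.

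**It is one secondary endpoint.** This also stands. The primary endpoint is untouched, and ICU admission is not named in any secondary objective in section 2.

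**Organ failure.** A reader might infer that this composite is biased the other way, against the guided arm, because the algorithm prescribes the noradrenaline that it counts. The documents do not support that. Vasopressor use counts alike in both arms. The algorithm gives hypotensive responders another bolus instead, and control physicians may start vasopressors at their discretion, so the net difference in use is unknown. With 20% other organ failure, assuming 15% guided and 5% control use gives 0.15 + 0.85 × 0.20 = 32% against 0.05 + 0.95 × 0.20 = 24%. Exchanging the two shares reverses the sign.

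**Conclusion.** The point holds for ICU admission. The endpoint carries a post-randomisation exclusion that contradicts the analysis population in section 9 and, on the likeliest reading, acts in the guided arm only. It then favours that arm whenever the excluded patients have above-average ICU risk, whether they leave the denominator or are counted as non-events. With 20% true risk in both arms, 10% excluded and 60–80% of those admitted, removal gives a reported 13–16% in the guided arm. The size rests wholly on assumed rates. The direction rests on the guided-arm reading and, for removal, on pv > p.

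Two further inferences go too far. The excluded patients are hypotensive fluid non-responders; that they are the sickest in the arm is not stated. Nor does it follow that neither ICU admission nor organ failure could support a conclusion: the first is repaired by a change of wording, and no bias is shown in the second.

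**What to change.** - Delete the exclusion and define the endpoint as ICU admission within 7 days in all randomised patients of both arms.
- Report the reason for admission (vasopressor only or other) descriptively in both arms. This serves the exclusion's likely purpose.
- If a restricted version is wanted, keep it as a sensitivity analysis. Define *protocolized* so that the restriction is identical in both arms, and state whether restricted subjects leave the denominator.
- For new-onset organ failure, at most report the composite by component as well, because vasopressor use is partly set by the guided-arm algorithm.

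The change should be made before the arms are compared. Table 1 already collects hospital and ICU admission, organ support and vasopressor data; the reason for admission may need one recorded item or derivation from these. The downside is that the guided arm's ICU rate may look less favourable, because it will include transfers made only to give protocol noradrenaline. The reason-for-admission table lets a reader see how many there were.

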The **Starling SV monitor** is a state-of-the-art technology that provides continuous, real-time information on cardiac index, cardiac output, stroke volume index, and total peripheral resistance. (12) This system is capable of detecting cardiovascular changes in sepsis and guiding hemodynamic resuscitation for individual septic patients. (13) Evidence to date, however, is limited to severely ill patients where intensive care unit (ICU) admission was already foreseen (6), where already a relevant amount of fluids was administered. (14) Although feasibility at the emergency department (ED) has been demonstrated, (15) the added value for clinical decision making has not yet been established. (16)

Based on the pathophysiological cardiovascular changes in early sepsis, **we hypothesize that point-of-care measurements of stroke volume (SV), cardiac output (CO) and total peripheral resistance (TPR) by the Starling SV monitor can be used to expand our understanding of interindividual differences in the clinical course of sepsis and develop personalized resuscitation plans for patients with sepsis at the ED.** Therefore, the primary objective of the current project is to assess the effect of the personalized hemodynamic resuscitation protocol guided by the Starling SV monitor on the volume (in liters) of intravenous (IV) fluid resuscitation within the first three hours of their emergency department (ED) admission.

Since most sepsis patients are admitted to the general ward, rather than ICU, we will focus on patients with sepsis that are admitted via the emergency department. With its potential to improve outcomes for sepsis patients, this innovative technology has the potential to optimize the management of this life-threatening condition. We decided to focus on the first three hours of hemodynamic resuscitation, which is the period when - currently - patients receive one-size-fits-all fluid resuscitation per protocol, which may be followed by the start of vasopressors at the ICU. We expect that personalized hemodynamic resuscitation using non-invasive CO and TPR measurements during the initial resuscitation at the ED and the following three hours, will

reveal to be an efficacious strategy to reduce the time to hemodynamic stability, while limiting the risk of overhydration.

Copy

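### Hemodynamic stability can be met on a running vasopressor whose rule differs by arm, and the same protocolized drug counts as new organ failure but is carved out of ICU admission

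*Protocol*

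**What the plan says.** **The endpoints.** Section 8.1.2 (Efficacy, hemodynamic resuscitation) has two HDS endpoints: "Time to recovery of normal perfusion/hemodynamic stability (HDS" and "Proportion of patients reaching normal perfusion/hemodynamic stability" within three hours. The footnote beginning "Hemodynamic stability (HSD) is defined as MAP" requires four values together: MAP at least 70 mmHg, SBP at least 90 mmHg, lactate at most 4 mmol/L and shock index at most 0.9. It does not mention vasopressors and sets no minimum duration.

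**Other rows of the same table.** New onset organ failure within 48 hours is met by a SOFA rise of at least 2 or by "Organ support (i.e. vasopressor use [non-]invasive mechanical ventilation, acute dialysis, ECMO". The hospital-admission row has "ICU admission within 7 days (excluding subjects receiving protocolized vasopressor therapy".

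**The treatment rules.** In section 5.1 (Intervention), a guided patient with MAP below 65 or SBP below 90 falls under this rule: "Not fluid responsive (on last measurement): patients will receive vasopressor (noradrenaline), according to the standard care protocol". Section 5.1 (Control) mandates no therapeutic protocol. Section 3 (Groups) allows fluids, vasopressors or both in the control arm during the first three hours. Section 1 describes current care as fluids per protocol, "which may be followed by the start of vasopressors at the ICU".

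**The concern.** The endpoint's label speaks of recovered perfusion, but a patient whose pressure is held up by an infusion can meet the definition. This would matter less if both arms followed the same vasopressor rule. Here the rule is part of what is randomized: required for one type of guided patient, discretionary in control.

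Section 1 expects the strategy to shorten time to hemodynamic stability while limiting overhydration, and the HDS endpoints carry the first half of that claim. As they stand, a faster or more frequent HDS in the guided arm cannot be told apart from earlier drug support.

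The organ-failure endpoint has the mirror problem. If more guided patients receive the drug because the algorithm requires it, that arm collects more organ-failure events for following its assignment. The sponsor protected the ICU-admission endpoint against protocolized vasopressor use but left organ failure unprotected, so two rows of one table treat the same drug use differently.

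**Working it through.** **1. What the plan computes.** The protocol gives no HDS rate, no vasopressor rate and no power for HDS. Its only computed figure is the sample size for the primary endpoint in section 4.4. That figure reproduces: with SDs of 2.85 and 3.44 L and a difference of 1.37 L, Welch power at 85 per arm is 80.25%. It has no bearing on HDS beyond the planned 94 per arm.

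**2. Can the drug satisfy the definition?** It can act on three of the four components. It raises MAP and SBP directly, and raising SBP lowers the shock index through its denominator. At a heart rate of 100, for example, a shock index of 0.9 needs SBP of at least 100 / 0.9 = 111.1 mmHg. Lactate, the fourth component, is not set by pressure.

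**3. Does the guided rule by itself deliver HDS?** No.
- The drug is triggered at MAP below 65 or SBP below 90, while HDS needs MAP of at least 70 together with the shock index and lactate conditions.
- A guided non-responder who is not hypotensive but has shock index above 0.9 waits 30 minutes, then has only optional fluid under the rescue rules (section 5.1). That branch can lower the guided HDS rate.
- Control patients may receive vasopressors too.

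**4. Illustration of size (all inputs assumed).** Let v be the excess share of guided patients on a vasopressor and c the share of those who meet HDS only because of it. Let w be the share of guided patients in the 30-minute-wait branch and l the fraction of them who miss HDS as a result. The shift in the guided HDS proportion is v × c − w × l.

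| v | c | w | l | Shift (points) |
|---|---|---|---|---|
| 5% | 25% | 0 | – | +1.25 |
| 10% | 50% | 0 | – | +5 |
| 20% | 50% | 0 | – | +10 |
| 10% | 50% | 10% | 50% | 5 − 5 = 0 |
| 10% | 50% | 30% | 30% | 5 − 9 = −4 |

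**5. What an upward shift could do.** Take 94 per arm, 50% HDS in control and no other difference between arms. The chance of p < 0.05 favouring the guided arm is Φ[(Δ − 1.96 × SE0) / SE1]. For Δ = 0.10:
- SE0 = √(2 × 0.55 × 0.45 / 94) = 0.0726
- SE1 = √((0.25 + 0.24) / 94) = 0.0722
- Φ[(0.10 − 0.1422) / 0.0722] = Φ(−0.585) = 27.9%

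The same formula gives about 10% for a 5-point shift and about 4% for 1.25 points, against 2.5% in that direction with no shift. Moving the control rate between 40% and 60% changes the 10-point result only to 28–30%.

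**6. The organ-failure row.** No arithmetic applies. Protocolized vasopressor use is excluded from ICU admission, but organ failure counts any vasopressor use within 48 hours without exclusion. Both endpoints sit in the same efficacy table.

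**The case against.** **The effect is the intended mechanism.** The strategy chooses between fluid and vasopressor, so reaching stability with noradrenaline instead of more fluid is one way it is meant to work. The HDS thresholds also mirror most of the entry criteria in section 4.2, so the endpoint coherently measures reversal of the qualifying abnormality. This stands as a reason to keep the definition. It does not justify reading the result as recovery of normal perfusion when support status is not shown.

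**Vasopressor use is already visible.** Section 8.1.2 (Safety) lists vasopressor therapy within three hours and time to vasopressor, and section 9.2 leaves binary and time-to-event analyses to a later plan. But those endpoints give only overall rates per arm and do not show which HDS successes were supported. The HDS definition itself is fixed in the protocol.

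**A vasopressor-free definition would bring its own bias.** It would score guided patients as failures for following their rule, while control patients held up by large fluid volumes would count as recovered. This stands, and it is why a sensitivity analysis is preferable to a redefinition.

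**Recovered and organ failure is not a contradiction.** A reader might infer that one patient cannot be both. The endpoints measure different things over different windows, and a stabilized patient may also have needed support. What does need reconciling is the unequal handling of protocolized vasopressors between the ICU-admission and organ-failure rows.

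**Conclusion.** The point holds in limited form. HDS can be met on a running vasopressor, and the rule for giving that drug differs by arm, so a difference in HDS can partly reflect drug-supported pressure. A reader might infer that the drug rule necessarily raises the guided arm's stability rate. The documents do not support that, because lactate, the gap between the 65 and 70 mmHg thresholds, the 30-minute-wait branch and control-arm vasopressors all leave the net direction open.

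The range of about −4 to +10 points is an illustration. Every input is assumed, and more extreme inputs would widen it. The inconsistency in how protocolized vasopressor use is handled rests on the text alone and needs no assumption. How far it counts against the guided arm depends on how many more guided patients receive the drug.

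Only secondary endpoints are affected. The primary endpoint, IV fluid volume over three hours, is untouched, and HDS does not appear among the section 2 objectives.

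**What to change.** No treatment rule changes. In section 8.1.2, or in the analysis plan that section 9.2 announces:

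- Keep HDS as defined. Report three-hour status by arm in three levels: stable without vasopressor, stable on vasopressor, not stable. State whether the level is taken at the three-hour mark or when the definition is first met.
- Add a sensitivity analysis of time to HDS in which the four values count only without a running vasopressor, and acknowledge the trade-off described above.
- Report new onset organ failure as defined, and again without patients whose only qualifying event is protocolized vasopressor use, so that it can be read beside the ICU-admission endpoint. If the SOFA scoring used awards points for vasopressors, say how those points are handled.

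Table 1 in section 8.3 already collects vasopressor time, amount and type. The one thing to check is that stop times are captured as well as start times. The cost is a little more analysis and a guided-arm HDS result that may look less favourable.
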